## Allocation

The allocation of subjects to groups will be randomized. Randomization will be conducted by an investigator not involved in the study, using the OxMaR Spanish version tool for clinical trial randomization developed by Guillaumes & O'Callaghan [40].

## Outcome measures

The executive functions of the children will be assessed using neuropsychological tests that have established validity and reliability for this population and within the context of such studies. The selection of tests for this protocol was based on recommendations from Robledo et al. [39]).•**Planning**

To assess planning, the Tower of London test has been selected. This cognitive task, originally designed by Tim Shallice in 1982 and later constructed and validated by Culbertson & Zillmer [41], evaluates executive functions, particularly planning and problem-solving. The test requires participants to move a series of colored disks between three poles to achieve a specific configuration using the fewest possible moves. The task includes constraints such as limits on the number of disks that can be moved at once and rules prohibiting larger disks from being placed on top of smaller ones.•**Working memory**

Since working memory comprises various components, different measures were selected to assess each process. For verbal-auditory working memory, the Digit Span subtest of the WISC-V (Wechsler Intelligence Scale for Children, Fifth Edition) was chosen. This subtest includes two main parts: Forward Digit Span and Backward Digit Span [42]. In the Forward Digit Span task, the evaluator reads a series of numbers aloud at a steady pace, and the child repeats them in the same order they were presented. The length of the number sequences progressively increases from shorter to longer sequences. In the Backward Digit Span task, the procedure is similar, but the child is required to repeat the numbers in reverse order.

Spatial working memory will be assessed using the Corsi Block-Tapping Task, a component of the Wechsler Memory Scale III battery [43]. This task involves a set of identical blocks arranged in fixed positions with irregular distances between them [44]. During the task, the evaluator taps the blocks in a specific sequence, which the participant must then reproduce by tapping the blocks in the same order they were presented. The sequence length gradually increases throughout the task. Similar to the Digit Span test, the Corsi Block-Tapping Task includes two parts: in the first part, the participant taps the blocks in the same order as presented, and in the second part, they tap the blocks in reverse order.

For visual working memory, the Visual Span subtest of the WISC-V test battery [42] will be used. In this task, the child is shown a series of images in a specific order. Subsequently, a larger group of images is presented, and the child must identify the images and their sequence from the initial presentation. The number of images progressively increases throughout the task.•**Inhibitory control and cognitive flexibility**

To assess inhibitory control and cognitive flexibility, the classic Stroop test task was selected [45]. The Stroop Test evaluates interference control, mental flexibility, and attentional management. The test is based on the interference phenomenon, which occurs when processing one feature of a stimulus interferes with processing another. In the first part of the task, the subject is given a list of color words (blue, red, green) written in black ink and must read them in order. Next, a list of stimuli consisting of three letters 'X' printed in different colors is presented, and the subject must name the color of the ink. Finally, a list of color words (blue, red, green) printed in various colors is shown, and the subject must indicate the color of the ink without reading the word. The subject has 45 s to complete each list.

Another measure to assess cognitive flexibility will be the Wisconsin Card Sorting Test (WCST), a neuropsychological assessment tool that evaluates planning ability, cognitive flexibility, abstract reasoning, and problem-solving. A shortened version of 48 cards has been validated for use in children [46]. In this test, the subject must sort a series of cards that vary in color, shape, and number of figures. The goal is for the participant to identify a sorting rule that is not explicitly stated and that changes throughout the test. The challenge lies in the individual's ability to detect changes in the sorting rule and adapt to them flexibly.•**Attention**

For attention, two neuropsychological tests were selected: the d2 Attention Test and the Trail Making Test. The d2 Attention Test, developed by Rolf Brickenkamp [47], measures sustained attention and processing speed. It consists of a worksheet with several rows of the letters 'd' and 'p,' each accompanied by one, two, three, or four small dashes above or below. The task requires the participant to cross out all the 'd' letters with two dashes above or below, ignoring all other letters and marks. The activity is timed, with a 20-second limit for each row, and includes a total of 20 rows.

The Trail Making Test (TMT) [48] evaluates visual processing speed, sustained attention, and divided attention. The test consists of two parts: Part A involves a sheet with randomly distributed numbers that the subject must connect in ascending order as quickly as possible. Part B is similar to Part A but includes both letters and numbers. The subject must connect them in ascending order while alternating between numbers and letters [49]. For this study, the children's version of the TMT, which has fewer stimuli, will be used.•**Covariate measures**

Sociodemographic data for each participant will be collected through a sociodemographic characterization questionnaire. This questionnaire includes variables such as parents' level of education, access to technological and informational resources, family socioeconomic status, and family composition, among others. These data will be treated as covariates to observe the correlation of these variables with the performance of the participating children, thereby achieving better control of confounding variables.

## Interventions

•
**Experimental group**

The experimental group will participate in computerized cognitive training. The intervention will take place in the computer lab of the participating educational institution. Each session will last 40 min, with a frequency of two times per week, for a duration of eight weeks, totaling 16 sessions.

For the development of the intervention, the digital platform 'NeuronUP' has been selected as the digital environment for cognitive stimulation and executive function training (see Fig. 2). NeuronUP is a cognitive rehabilitation and stimulation platform hosted on a cloud system, allowing access from any device via a web login [50]. In a systematic review by Guerrero & García [28], NeuronUP was analyzed and compared with other neuropsychological rehabilitation platforms. The authors found that NeuronUP had strengths in adaptability, flexibility, evidence of effectiveness, data management, and treatment, receiving a rating of 7.14 out of 10.

**Fig. 2 fig0002:**
[figure not shown]
Example activities from NeuronUP.

Launched in 2012, NeuronUP features a vast repository of digital activities designed to customize sessions according to the needs of each participant. These activities are contextualized to daily life situations related to functionality variables, ensuring ecological validity. They are based on strong theoretical frameworks and principles of neuropsychological habilitation and rehabilitation [50]. Many activities mimic paradigms similar to classic tasks (e.g., go/no go, Flanker, Stroop, among others). The platform consists of two sections:(1)Activity Manager: It contains categorized material for conducting sessions.(2)Results Manager: It stores the results of all activities performed by participants.

The activities adapt to the child's performance, increasing or decreasing in difficulty according to the child's needs. They are divided into three types: generators, games, and sheets.-Generators are unlimited and ecological activities that prevent users from memorizing the exercise, encouraging them to focus on the process by creating endless versions of the same activity. These can be executed digitally or on paper and are highly customizable to facilitate the introduction of meaningful stimuli.-Games are activities organized into different levels of difficulty, allowing users to advance or regress automatically based on their successes or errors. They can also be customized to suit each user's needs.-Sheets are activities organized by levels of difficulty. They can be worked with correction, meaning the platform corrects the user after each action, or in a free manner, where the platform does not provide feedback until the end of the exercise, not indicating whether the user is right or wrong during the activity.

The platform includes various intervention areas such as cognitive functions, activities of daily living, and social skills. For the purposes of the current research, activities were selected to train executive functions (working memory, planning, flexibility, inhibition) and attention.

The researchers reviewed the available activities, and after a pilot exercise, 54 activities are selected and distributed across the 16 sessions. Each session consists of 8 activities, each programmed for 5 min, for a total of 40 min per session. Although each digital activity contributes to the training of various cognitive functions, activities with an emphasis on one cognitive process are selected for each session. Accordingly, the 16 sessions are distributed with the following emphasis: 4 sessions for working memory, 4 sessions for planning, 4 sessions for attention, and 4 sessions for inhibitory control and cognitive flexibility (the latter processes are integrated due to the lower number of available activities). Fig. 3 presents the selected digital activities from the NeuronUP platform, differentiating by type of activity (game, worksheet, and generator), the cognitive processes they train, and the session in which they are introduced.•**Control group**

**Fig. 3 fig0003:**
[figure not shown]
Selected activities and structure of digital sessions.

For the study, an active control group is selected. One benefit of an active control group is that it helps control for positive beliefs participants may have about the intervention's use, thereby reducing biases. It also enables blinding of participants who are not informed about which intervention is the study's target [51].

The active control group will receive cognitive training based on paper-and-pencil exercises. This intervention has the same frequency and duration as the experimental group's intervention, with 2 sessions per week for 8 weeks. The intervention for the active control group will follow the same structure and objective as the experimental group's intervention. Therefore, the paper-and-pencil exercises selected for each session aims to train the same cognitive processes as the experimental group's sessions. Out of the 16 sessions, 4 emphasize working memory, 4 emphasize planning, 4 emphasize attention, and the remaining 4 emphasize flexibility and inhibition, as shown in Fig. 4.

**Fig. 4 fig0004:**
[figure not shown]
Example activities from eCognitiva.

For the paper-and-pencil sessions, freely available activities are selected. One of the sources is the cognitive stimulation worksheets and exercises from the eCognitiva.com website (See Fig. 4). This website offers workbooks focused on different cognitive domains such as attention, memory, language, and arithmetic (eCognitiva, n.d.). While the website provides materials for children [52] and adults with cognitive impairment [53], these materials can easily be adapted for other populations. Therefore, the researchers select them from the various available workbooks and distribute them across the different cognitive domains addressed in the study. Additionally, some paper-and-pencil activities designed by the researchers in previous studies [54] are adapted, as well as activities from other cognitive stimulation programs [55].

## Bias control

For bias control, we rely on the bias control tool for controlled trials from the Cochrane organization [56], which defines six domains of bias (see Table 2). We established actions to control the occurrence of the most common types of bias in non-clinical studies, such as selection bias, detection bias, performance bias, attrition bias, and reporting bias [20].

**Table 2 tbl0002:** Risk of Bias Control.

Domain	Mechanism to reduce bias risk
Selection bias	Subjects will be randomly assigned through an online randomization software, with this procedure being overseen by an external researcher.
Performance bias	The researchers responsible for the intervention will be blinded to the assignment and test results. Both the control and experimental groups will participate in an intervention; therefore, the participants will be blinded to the target intervention.
Detection bias	The researcher responsible for administering the pre-test and post-test measures will be blinded to the assignment.
Attrition bias	An intention-to-treat analysis approach will be used. Therefore, instead of excluding participants who did not complete the intervention, all participants will be included in the analysis. Synthetic data imputations will be conducted to project missing data, and subsequently, these results will be compared with the per-protocol analysis, which excludes missing data.
Reporting bias	The results will be published according to the objectives outlined in the protocol, regardless of whether the results confirm the proposed hypothesis or not.

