## Abstract

The research aims to evaluate the effectiveness of a computerized cognitive training program in improving executive functions and attention in elementary school children, compared to a traditional paper-and-pencil intervention. The study has been formulated as a randomized controlled trial with pre- and post-intervention measures. For the study, third-grade children with typical development aged between 7 and 9 years will be recruited. Participants will be randomly assigned to the two study arms (control and experimental). The experimental group will participate in a computerized intervention using the NeuronUp cognitive stimulation platform for 8 weeks, twice a week. Sessions will be conducted using computers in the computer lab of the participating educational institution. The active control group will engage in paper-and-pencil cognitive training for the same duration and intensity as the experimental group. Evaluators will be blinded to the assignment, and participants will be blinded to the target intervention. Hypothesis testing will be conducted through ANOVA-MR, and logistic regressions will be implemented to assess the effect of socioeconomic variables on children's performance. These results are expected to contribute to the discussion on the opportunities and benefits offered by cognitive training programs on the cognitive development of typically developing children.

Specifications table

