**Table utbl0001:** 

Subject Area:	• Cognitive sciences
More specific subject area:	• Children's Cognitive Development
Name of your method:	Randomized controlled trial to evaluate the effect of a cognitive training program
Protocol name:	Effects of computer-based cognitive training vs. paper-and-pencil-based training on the cognitive development of typically developing children: Protocol for a randomized controlled trial.
Reagents/tools:	• Computer-based cognitive training • Paper-and-pencil cognitive training
Experimental design:	A randomized controlled trial with intra-subject and inter-subject evaluations will feature two parallel groups: an experimental group and an active control group. Pre-test and post-test measures will be conducted. Participants will consist of two third-grade classes, aged 7 to 10 years (*N* = 58). Random allocation will be employed. Primary measures will include neuropsychological tests to assess executive functions (cognitive flexibility, working memory, inhibitory control, planning, and attention). The experimental group will undergo computer-based cognitive training, while the control group will undergo paper-and-pencil cognitive training. The intervention will take place at the educational institution, twice a week in 40-minute sessions, spanning 8 weeks with a total of 16 sessions. Evaluators responsible for pre-test and post-test measurements will be blinded to the allocation. Researchers in charge of the intervention will be blinded to the evaluation results.
Trial registration:	The study was registered in the Office of Research and Scientific Development at University of Tolima under code 50,119.
Ethics:	The randomized controlled trial complies with the ethical parameters defined by the Helsinki Declaration [1], as well as the norms for health research established by the Colombian Ministry of Health [2] in Resolution 8430. Parents and guardians of the children who agree to participate will sign informed consent forms. This randomized controlled trial has been approved by the bioethics committee of University of Tolima, as documented in minutes No. 10 of December 13, 2022.

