## Protocol validation

This article presents the protocol of a randomized controlled trial aimed at evaluating the effects of computerized cognitive training on executive functions and attention in school-aged children, compared to traditional pencil-and-paper cognitive training. The study is relevant and pertinent to the academic community for several reasons: 1) It contributes to the discussion on integrating cognitive training into school activities to support children's cognitive development. 2) It will help consolidate evidence on the impact of computerized cognitive training and pencil-and-paper training in typically developing school-aged children. 3) It explores whether the use of technological interventions in cognitive training yields different impacts compared to non-digital interventions. 4) It assesses the feasibility of integrating cognitive training programs into primary school curricula. 5) The designed protocol aims to ensure the quality of the collected evidence through thorough bias control. Among the measures to be implemented for bias control are blinding of evaluators to assignment, blinding of researchers responsible for the intervention to subject evaluation, blinding of participants to the target intervention, and randomization of subjects to both study arms. Synthetic data imputations will be employed to handle missing data in the study, opting for intention-to-treat analysis.

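### Table 2 claims that those who deliver the training are blinded to assignment, which computer versus paper sessions do not allow and which goes further than the article's other blinding statements

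*Protocol article*

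**What the plan says.** The article describes the blinding of the staff who run the training in three places.

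- Bias control, Table 2, performance-bias row: "The researchers responsible for the intervention will be blinded to the assignment and test results".
- Specifications table, experimental design entry: "Researchers in charge of the intervention will be blinded to the evaluation results".
- Protocol validation, in the list of bias-control measures: "blinding of researchers responsible for the intervention to subject evaluation".

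The Abstract summarises blinding without mentioning these staff: "Evaluators will be blinded to the assignment, and participants will be blinded to the target intervention". The same Table 2 row gives a second measure: "Both the control and experimental groups will participate in an intervention; therefore, the participants will be blinded to the target intervention".

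The two trainings are described under Interventions. For the experimental group: "The intervention will take place in the computer lab of the participating educational institution". For the control group: "The active control group will receive cognitive training based on paper-and-pencil exercises". The control text adds that the paper sessions match the digital ones in frequency, duration, structure and the cognitive processes trained.

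**The concern.** Table 2 is the article's risk-of-bias statement and is modelled on the Cochrane tool. Blinding of deliverers to assignment is the first mechanism it lists against performance bias. Whoever supervises a NeuronUP session or hands out worksheets knows which training the children are receiving, so the design cannot have this property.

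What is at stake is the interpretation of the arm difference. The trial compares two modes of delivery, and how staff encourage, explain and manage the children in each mode is part of what could produce a difference. If the Table 2 sentence passes into the trial report, readers will be told that personnel were blinded and will discount a source of bias that is in fact open.

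**Working it through.** No arithmetic applies: the point rests on no effect size, error rate or sample size. The check compares the blinding statements with each other and then with the two interventions.

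**Step 1. Who is blinded to what.**

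| Place in the Protocol article | Those delivering the training | Those testing the children |
|---|---|---|
| Abstract | not mentioned | assignment |
| Specifications table | evaluation results | allocation |
| Table 2 | assignment and test results | assignment |
| Protocol validation | evaluation of the children | assignment |

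For the evaluators, all four places agree; the Specifications table, for example, has "Evaluators responsible for pre-test and post-test measurements will be blinded to the allocation". For the deliverers, three places speak, and only Table 2 includes assignment. Protocol validation lists the two roles one after the other and gives each a different blinding: evaluators to assignment, deliverers to the evaluation. On that scheme, blinding to assignment belongs to the evaluators.

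**Step 2. Whether each element of the Table 2 sentence can be met.**

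- *Test results.* Yes. Testing and training are separate roles, and scores can be withheld from the people running sessions. All three places agree on this.
- *Assignment.* No. The arms differ in the visible medium at every one of the 16 sessions: a digital platform on computers against exercises on paper. Running a session of either kind reveals the arm.

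**Step 3. Whether another meaning of the phrase would rescue it.** Concealment of the allocation sequence is covered elsewhere, under Allocation and in the selection-bias row of Table 2. Not knowing which training is the target is claimed in the same row, but for the children. Neither is what the sentence says about the deliverers.

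**Step 4. What the remaining measures cover.**

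| Measure | What it guards against | Covers deliverers who know the arm? |
|---|---|---|
| Deliverers blinded to test results | Adjusting the training in response to a child's scores | No |
| Active control with matched sessions | Differences in contact time, structure and content focus | No |
| Children unaware of the target training | Differences in the children's expectations | No |
| Evaluators blinded to assignment | Biased testing (detection bias, a separate row) | No |

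One element of the performance-bias row therefore fails, and nothing else listed takes its place.

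**The case against.** The strongest reply is that this is a slip of wording in one table cell. The Specifications table and Protocol validation already give a feasible version, the evaluators are consistently blinded, and the comparator is well matched. Most of this stands. It limits the weight of the point but does not make the Table 2 sentence true.

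Several stronger readings are tempting, and the documents do not support them.

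- *That Table 2 is contradicted by the other two places.* They state a narrower blinding. Neither says that the deliverers know the assignment. The texts are inconsistent in scope, not opposed.
- *That performance bias is not controlled at all.* Three measures remain: blinding to test results, the matched active control, and children unaware of the target training.
- *That the deliverers favour the digital arm.* The background section does list advantages of computerized training, but it also says that this training need not replace paper exercises, and the hypotheses allow superiority in either direction. Deliverers' expectations are not described.
- *That each arm has its own staff, so that a staff effect is mixed with the training mode.* The article does not say how sessions are staffed. A condensed article may leave this to the full protocol, so its absence is no fault. Any figure for such an effect would be invented.

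**Conclusion.** The point holds in a limited form. Table 2 states a blinding of deliverers to assignment that the design cannot provide and that goes beyond the article's other two statements about the same staff. The other measures in the row remain valid, but none addresses deliverers who know the arm.

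The size of any resulting bias, and its direction, cannot be derived from the document. The conclusion assumes only that assignment means the child's training arm and that the staff named in the row are those who run the sessions. It does not touch the sample size, the randomization, the blinding of outcome evaluators or the analysis. What changes is what the trial may claim about performance bias. The correction should be made, but the error is not fatal to the trial.

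**What to change.** 1. In Table 2, performance-bias row, limit the statement about the deliverers to blinding to test results, in line with the Specifications table and Protocol validation.
2. State there that deliverers know the assignment and that only the outcome evaluators are blinded to it.
3. Acknowledge the residual performance bias from unblinded deliverers, and carry that caveat into the interpretation of the arm difference.

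An optional safeguard, where existing staffing allows, is to have the same facilitators run sessions in both arms. The correction does not depend on it.

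The cost is a few sentences and a slightly less favourable risk-of-bias statement.

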## Sample size calculation

A projected estimate was conducted using G-Power to establish parameters for sample size calculation (see Table 1), based on previous studies that reported moderate to large effect sizes in similar research [39]. This estimation suggests a group size of 29 children, resulting in a total sample size of 58 children.

**Table 1 tbl0001:** Parameters for group size calculation.

Parameter	Value
Effect size	0,75
α confidence level	0,05
Sample power	0,8
Number of groups	2
Number of measures	2
Total sample size	*N* = 58
Sample size per group	*N* = 29

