## Statistical analysis plan

A hypothesis test will be conducted using Mixed-Model Analysis of Variance of Repeated Measures (RM-ANOVA), followed by Bonferroni corrections to examine differences between groups. In this analysis, pre-test and post-test evaluations will act as the within-subject factor (repeated measures), while the comparison between the experimental and control groups will serve as the between-subject factor. Partial eta squared will be used to quantify effect size, assuming variables meet the assumptions of homoscedasticity and normality for parametric tests; otherwise, non-parametric tests will be employed.

To analyze the relationship between participants' performance and various sociodemographic variables acting as potential confounders, multivariate linear regression analysis will be conducted for numerical variables, and logistic regression analysis will be applied for categorical variables.

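### The 'per-protocol' analysis is defined as the one without missing data, so it is a complete-case check and says nothing about adherence

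*Protocol article*

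**What the plan says.** Table 2 of the protocol article (Bias control, attrition bias) adopts intention-to-treat: "instead of excluding participants who did not complete the intervention, all participants will be included in the analysis". It then says "Synthetic data imputations will be conducted to project missing data", and that "these results will be compared with the per-protocol analysis, which excludes missing data". The last clause is the only description of the per-protocol set anywhere in the article. No minimum attendance or other adherence criterion is attached to it.

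The section Protocol validation repeats the approach: "Synthetic data imputations will be employed to handle missing data in the study, opting for intention-to-treat analysis". Neither place says whether imputation is single or multiple, under what model, or how results are pooled.

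The planned amount of training is stated exactly under Interventions: "Each session will last 40 min, with a frequency of two times per week, for a duration of eight weeks, totaling 16 sessions". The control arm has the same frequency and duration, so there is a clear yardstick for adherence.

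The section Statistical analysis plan names a mixed repeated-measures ANOVA with two groups and two time points.

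**The concern.** Failing to complete the training and lacking a test score are different events. The intention-to-treat sentence is about the first; the per-protocol clause is about the second. A per-protocol analysis is normally read as the effect among those who received the intervention as planned. A set selected on the presence of scores cannot answer that question.

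The risk lies in interpretation. If the two analyses agree, a reader will conclude that incomplete training made no difference, although attendance never entered the comparison. This matters in a trial of delivery modes. The Limitations section names school-calendar changes, device availability and internet quality as threats. The last two bear on the computerized arm, so the amount of training received could differ between arms.

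**Working it through.** **1. Who is in which set**

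| Sessions attended | Post-test | Intention-to-treat | 'Per-protocol' as written | Set defined by attendance |
|---|---|---|---|---|
| All 16 | taken | in | in | in |
| All 16 | missed | in, imputed | **out** | **in** |
| Few | taken | in | **in** | **out** |
| Few | missed | in, imputed | out | out |

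In the second and third rows the written rule gives the opposite of an attendance rule. In the limiting case where all 58 children take both tests, the written per-protocol set equals the intention-to-treat set whatever the attendance, and the two results agree by construction.

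**2. The plan's own figure**

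Inputs from Table 1: effect size 0.75, α 0.05, power 0.80, 29 per group. With a two-sided two-sample t-test (the article does not state the sides or the effect-size metric):

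- noncentrality = 0.75 × √(29/2) = 2.86, with 2 × 29 − 2 = 56 degrees of freedom;
- power = 0.801, and 29 is the smallest group size that reaches 0.80.

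The total of 58 is therefore reproduced. It is the figure for no lost scores.

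**3. What a single completion would do, if it were used**

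In a 2 × 2 repeated-measures ANOVA the group-by-time test is the t-test on change scores. With c = post − pre, the estimate is the difference in mean c between arms, and SE² = [(s₁² + s₂²)/2] × (2/29), on 56 degrees of freedom.

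Assumptions not in the article: post-tests missing completely at random at 10, 20 or 30% in each arm, and pre-post correlation 0.5 or 0.7. There were 4,000 simulated trials per setting with no true effect. Missing post-tests were filled from a regression on pre-test and arm in three ways:

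- the predicted value, once;
- a random draw, once;
- 20 draws pooled by Rubin's rules, T = W + (1 + 1/20)B, where W is the mean within-imputation variance and B the between-imputation variance.

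The SE ratio is the mean reported SE divided by the actual SD of the estimates. Ranges cover both correlations and, for a single completion, both ways of filling.

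| Missing | Scored per arm | Single: SE ratio | Single: type I | Multiple: SE ratio | Multiple: type I | Complete-case: type I | Complete-case: power at 0.75 |
|---|---|---|---|---|---|---|---|
| 10% | 26 | 0.894–0.929 | 0.068–0.078 | 0.989–1.011 | 0.045–0.052 | 0.046–0.053 | 0.76 |
| 20% | 23 | 0.819–0.846 | 0.094–0.109 | 0.995–1.010 | 0.047 | 0.047–0.050 | 0.70 |
| 30% | 20 | 0.731–0.759 | 0.136–0.147 | 0.997–1.029 | 0.041–0.052 | 0.046–0.052 | 0.64 |

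One setting in full (20% missing, correlation 0.7, one random draw): reported SE 0.2038, actual SD 0.2455, and 0.2038/0.2455 = 0.830, so the SE is 17% too small. Monte Carlo error on a 5% rejection rate is √(0.05 × 0.95/4000) ≈ 0.003.

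**The case against.** The clause sits in the attrition-bias row, where the purpose is to check the handling of missing data. A complete-case comparison does that, and the article nowhere claims to test adherence. The sentence before it contrasts intention-to-treat with leaving out children who did not finish the training, so the clause may be loose shorthand. A session threshold is also detail that a journal article can leave to a fuller plan.

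Much of this stands. The comparison is legitimate as a missing-data check, and the absence of a threshold alone would be no finding. What remains is that the article prints a definition, and that definition does not fit its name. A later analysis plan would have to repeat it or contradict it.

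Two stronger readings are tempting and are not supported:

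- A reader might infer that the main analysis will rest on one completed data set and so has inflated type I error. Both mentions use the plural, which is compatible with multiple imputation. Number, model and pooling are matters an article commonly leaves to a plan not shown here. Nothing says that one completed data set will be analysed.
- A reader might infer that children who stop the training will not be post-tested. The article does not say so, and keeping all participants in the analysis points the other way.

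**Conclusion.** The point holds for the per-protocol definition: as written it is a complete-case set, and its comparison with intention-to-treat is uninformative about adherence. This conclusion rests on the wording alone and needs no assumed figures. It concerns a secondary comparison; the primary intention-to-treat analysis and its conclusion are untouched.

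On imputation there is a question to settle and no stated error. The understatement of the standard error in the working would arise only with a single completion, and its size depends on the assumed missingness and correlation. Multiple imputation with Rubin's rules removes it.

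**What to change.** 1. Rename the analysis that excludes missing scores 'complete-case' and keep it as the check on the imputation.
2. Define the per-protocol set by sessions attended, with the minimum number of the 16 fixed by the sponsor before any post-test data are seen, and record attendance at each session in both arms.
3. Confirm that the synthetic data imputations are multiple imputations, and state that results are pooled by Rubin's rules.

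The cost is a change of wording, an attendance register and a little more analysis. The per-protocol set may be smaller and its estimate less precise. Recruitment, interventions and the primary analysis set do not change.
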